## Abstract

**Background:**

Approximately 70% of Australian adults aged over 50 are overweight or obese, with the prevalence significantly higher in regional/remote areas compared to cities. This study aims to determine if a low-cost, accessible lifestyle program targeting insufficiently active adults aged 50-69 y can be successfully implemented in a rural location, and whether its implementation will contribute to the reduction/prevention of metabolic syndrome, or other risk factors for type 2 diabetes, and cardiovascular disease.

**Methods/Design:**

This 6-month randomised controlled trial will consist of a nutrition, physical activity, and healthy weight intervention for 50–69 year-olds from a disadvantaged rural community. Five hundred participants with central obesity and at risk of metabolic syndrome will be recruited from Albany and surrounding areas in Western Australia (within a 50 kilometre radius of the town). They will be randomly assigned to either the intervention (n = 250) or wait-listed control group (n = 250). The theoretical concepts in the study utilise the Self-Determination Theory, complemented by Motivational Interviewing. The intervention will include a custom-designed booklet and interactive website that provides information, and encourages physical activity and nutrition goal setting, and healthy weight management. The booklet and website will be supplemented by an exercise chart, calendar, newsletters, resistance bands, accelerometers, and phone and email contact from program staff. Data will be collected at baseline and post-intervention.

**Discussion:**

This study aims to contribute to the prevention of metabolic syndrome and inter- related chronic illnesses: type 2 diabetes mellitus, cardiovascular disease, and some cancers; which are associated with overweight/obesity, physical inactivity, and poor diet. This large rural community-based trial will provide guidelines for recruitment, program development, implementation, and evaluation, and has the potential to translate findings into practice by expanding the program to other regional areas in Australia.

**Trial registration:**

Australian and New Zealand Clinical Trials Registry [ACTRN12614000512628, registration date 14^th^ May 2014].

**Electronic supplementary material:**

The online version of this article (doi:10.1186/s12889-015-1613-9) contains supplementary material, which is available to authorized users.

## Background

In Australia, approximately 70% of adults aged over 50 are overweight or obese, with the prevalence significantly higher in rural areas compared to metropolitan areas [1]. The prevalence of obesity has increased 8.8% in the last 17 years with poor diet and physical inactivity likely causes [2]. Overweight/obesity coupled with advancing age increases the risk of metabolic syndrome [3], which is a cluster of abnormalities that are well documented risk factors for type 2 diabetes mellitus and cardiovascular disease [4]. These include central obesity, elevated triglyceride levels, reduced high-density lipoprotein (HDL)-cholesterol, raised blood pressure, and raised fasting plasma glucose [5].

It is estimated that approximately 25% of the Australian adult population has metabolic syndrome [3]. Prevalence is age-dependent, with the incidence rising rapidly in those of middle-age [6,7]. The relative risk of type 2 diabetes mellitus in middle-aged adults and cardiovascular disease in men has been shown to increase among those with metabolic syndrome [8]. It is imperative that overweight/obese individuals, particularly those with metabolic syndrome, are identified to ensure risk factors are addressed through lifestyle modifications and management, thereby contributing to the reduction of type 2 diabetes mellitus, cardiovascular disease, and premature death [3,6].

The prevalence of overweight/obesity has been rising among middle-aged adults living in harder to reach and often neglected rural locations of Australia [2]. These people are more likely to be overweight/obese compared with adults living in cities [9], leading to higher levels of disease risk factors. The health profile of the Great Southern region of Western Australia (location of the study area – Albany) highlights the need for greater access to health services and programs to improve the health of residents. The majority of adults (89%) do not eat the recommended daily serves of vegetables, and almost half (47.8%) do not eat adequate amounts of fruit [10], while half (50.1%) of adults do not achieve the recommended levels of physical activity [10]. In addition, Albany scores 987.4 on the Socio-Economic Indexes for Areas, indicating relative disadvantage (<1000) [1]. More disadvantaged areas have higher prevalence of risk factors and reported ill health compared with less disadvantaged areas [1].

Currently, there is a gap in the knowledge for implementing effective home-based lifestyle interventions targeting chronic disease risk reduction in disadvantaged rural areas such as Albany. This paper describes the protocol of a randomised controlled trial (RCT) that aims to address metabolic syndrome and overweight/obesity by improving the physical activity and nutrition behaviours of insufficiently active middle-aged people residing in the rural town of Albany in Western Australia. It is hypothesised that by the end of the 6-month RCT, the intervention groups compared to the control groups will show significant improvements in insulin sensitivity and lipid profile, as well as a number of anthropometric, physical activity and nutrition outcomes; thereby reducing the risk of metabolic syndrome and chronic diseases.

## Methods

### Study design

This 6-month RCT will identify and recruit insufficiently active adults aged 50 to 69 with central obesity, residing in Albany, Western Australia, to participate in a home-based physical activity, nutrition, and healthy weight management intervention. Additional file 1: Figure S1 summarises the study design. A total of 500 participants with or at risk of metabolic syndrome will be recruited and randomised into intervention (n = 250) and wait-listed control (n = 250) groups. Data will be collected from both groups at baseline and 6 months to assess changes in outcome measures. Ethical approval of the study has been obtained from the Human Research Ethics Committee of Curtin University (HR149_2013). All participants will be informed of the research aims and objectives, and that confidentiality will be maintained throughout the study. Information and consent forms will be provided prior to entry into the RCT and participants will be free to withdraw from the program at any time.

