### Recruitment

Study participants aged 50–69 years and insufficiently active (less than 150 minutes of moderate physical activity per week) [11] will be recruited. Additional criteria for metabolic syndrome is based on assessing the following International Diabetes Federation (IDF) metabolic syndrome criteria [5]: central obesity (waist circumference >94 cm men or >80 cm women [Europids, Sub-Saharan Africans, Eastern Mediterranean, Middle East]; >90 cm men or >80 cm women [South Asians, Chinese, Japanese]); plus any two of: raised triglyceride level (>1.7 mM, or treatment for this); reduced HDL-cholesterol (<1.03 mM in males and <1.29 mM in females, or treatment for this); raised blood pressure (systolic ≥130 mmHg or diastolic ≥85 mmHg, or treatment of previously diagnosed hypertension); raised fasting plasma glucose (≥5.6 mM). However, only one instead of two of the latter four conditions needs to be satisfied to increase the potential pool of at risk participants. Identifying participants at risk of developing metabolic syndrome will enable appropriate intervention to be implemented, with the aim of preventing the onset of the syndrome and potential for type 2 diabetes and cardiovascular disease [12].

The following exclusion criteria will apply: previous diagnosis of diabetes mellitus (other than gestational diabetes); receiving treatment to lower blood glucose; on a weight loss diet or having weight fluctuations of >5% within the past 6 months; involvement in another physical activity and/or nutrition program; or a partner/individual residing in the same household as another participant already recruited for the study (to avoid contamination).

After the initial screening (n = 1000), it is expected that 625 participants will be eligible to join the study. Allowing for a subsequent 5% withdrawal rate and another 15% loss to follow-up, a final sample size of n = 250 intervention and n = 250 controls is anticipated, with quota sampling to ensure equal numbers of males and females. These figures are based on the pilot recruitment and data collection phase of the study.

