### Sample size

The power calculations are based on a logistic mixed regression model with the outcome variable being the prevalence of physical activity participation. Assuming 80% complete data across the assessments due to attrition and non-respondents, a total of n = 625 subjects satisfying the selection criteria will be initially recruited. In the power analyses, effect sizes of interest are associated with the time (pre-post) and intervention group parameters. For the mixed regression analysis, a final sample size of n = 500 [125 per gender by intervention condition] will provide sufficient power (80%) to detect a medium effect size at 5% significance level for the group by time interaction term accounting for gender but without other covariate adjustment.

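### 500 (250 per arm) is given both as the number randomised and as the number left after 20% attrition from 625, and only the second carries the stated 80% power

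*Protocol article*

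**What the plan says.** Two parts of the article give 500 as the size at entry.

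- Study design: "A total of 500 participants with or at risk of metabolic syndrome will be recruited and randomised into intervention", with the control arm listed next at the same size, 250 each.
- Abstract, Methods/Design: "They will be randomly assigned to either the intervention (n = 250) or wait-listed control group (n = 250").

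Two other parts give 500 as the size at the end.

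- Recruitment: after 1000 people are screened, "it is expected that 625 participants will be eligible to join the study". It continues: "Allowing for a subsequent 5% withdrawal rate and another 15% loss to follow-up", and then "a final sample size of n = 250 intervention and n = 250 controls is anticipated".
- Sample size: the stated assumption is "Assuming 80% complete data across the assessments due to attrition and non-respondents". On that basis the section says that "a total of n = 625 subjects satisfying the selection criteria will be initially recruited". The power claim follows: "a final sample size of n = 500 [125 per gender by intervention condition] will provide sufficient power (80"%) for a medium effect on the group-by-time interaction at the 5% level.

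The Control group section also gives n = 250 but does not say at which stage.

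**The concern.** The same figure, 250 per arm, stands for two quantities that differ by the whole attrition allowance. The verb is shared too: 500 are recruited in Study design and 625 in Sample size.

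The number to randomise tells the trial team when to stop enrolling, and the two readings differ by 125 people. A team working from Study design or the Abstract would stop at 500 and finish with fewer complete cases than the power statement needs. A team working from Sample size would go on to 625.

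**Working it through.** **Inputs**
- Final sample for the power claim: 500, i.e. 250 per arm and 125 per gender-by-arm cell (Sample size).
- Complete-data proportion: 80% (Sample size), split as 5% withdrawal and 15% loss to follow-up (Recruitment).
- Number initially recruited: 625 (Sample size). The same 625 is the number expected to be eligible (Recruitment).
- Number randomised: 500 (Study design, Abstract).
- Significance level 5%. Sidedness is not stated, so two-sided is assumed.

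**Step 1: reproduce the plan's figure.** Number to recruit = final N / (1 − attrition) = 500 / 0.80 = 625, an exact match. Applying the two losses in sequence gives 625 × 0.95 × 0.85 = 504.7, which also agrees for practical purposes. The inflation is correct, and it makes 500 the post-attrition number.

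**Step 2: can the losses fall before randomisation?** The text places them largely or wholly afterwards.
- The end of the Procedure section randomises people once eligibility is established. It describes no run-in in which 125 eligible people could leave.
- Sample size refers to complete data over the assessments, which Study design sets at baseline and 6 months.
- Statistical analysis speaks of attrition and withdrawal from the RCT itself.
- Process evaluation counts non-completers within the intervention group and asks why they withdrew.

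Loss to follow-up cannot precede entry. If the whole 5% withdrew before allocation, the number randomised would be 625 × 0.95 = 594, not 500.

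**Step 3: completers if 500 are randomised.**
- Full 20% after randomisation: 500 × 0.80 = 400 (200 per arm, 100 per gender-by-arm cell). In sequence: 500 × 0.95 × 0.85 = 404.
- Only the 15% after randomisation: 500 × 0.85 = 425.

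**Step 4: power on the plan's own terms.** Take it as given that 500 completers yield exactly 80%. The standardised effect at 500 is then 1.960 + 0.842 = 2.802, and it scales with the square root of the sample size: power = Φ(2.802 × √(n/500) − 1.960).

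| Completers | Calculation | Power |
|---|---|---|
| 500 | Φ(2.802 − 1.960) | 80% |
| 425 | Φ(2.802 × 0.922 − 1.960) = Φ(0.623) | 73% |
| 404 | Φ(2.802 × 0.899 − 1.960) | 71% |
| 400 | Φ(2.802 × 0.894 − 1.960) = Φ(0.546) | 71% |

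A one-sided test would give 72% at 400. At 400 completers, the effect detectable with 80% power, on whatever scale the plan used, is larger by a factor √(500/400) = 1.12.

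**Step 5: does the scaling suit a binary outcome?** It was checked with an approximate difference-in-differences on the logit scale, for assumed baseline prevalences of 20%, 30% and 50% and within-person correlations of 0, 0.3 and 0.5. In all nine cases, the odds ratio giving 80% at 250 per arm gave 70.7% at 200 per arm.

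**Step 6: how far does this depend on the 80% being exact?** The 80% cannot be derived, because no effect, prevalence or correlation is given. As an illustration only, suppose medium means 0.5 SD on a continuous outcome with zero within-person correlation, so that the SD of change is √2. Then power = Φ(0.5 / (√2 × √(2/n)) − 1.960) for n per arm.
- Whole sample: 97.7% at 250 per arm, 94.2% at 200.
- Within one gender: 79.8% at 125 per arm, 70.5% at 100.

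So the consequence runs from slight to about nine points, depending on what the plan meant.

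**The case against.** The strongest defence is that the two sections that derive the sample size agree with each other: 625 at the start, 500 at the end. On that view, Study design and the Abstract merely reuse the final target as a headline figure, and nobody who read Sample size would stop at 500. This makes 625 the likely intention, but it does not remove the conflict. Study design says outright that 500 are randomised, and it is the natural place to look for that number.

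Other parts of the defence stand and limit the point.

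- A reader might infer that the article states 625 as the number randomised. It does not: 625 are eligible or initially recruited. Eligibility and baseline measurements come before allocation, so some of the 5% could be lost first. That is why 425 is shown beside 400.
- A reader might infer that the 80% power is simply lost. The article does not support that, because the claim rests on an unquantified effect; Step 6 shows that ample power could remain.
- A reader might restate the shortfall as a detectable difference in SD units between two means. That does not match the stated basis, which is a binary outcome in a logistic mixed model.
- A reader might add that the intention-to-treat population is undefined. That would be the same inconsistency again, not a second one, and an article may leave analysis sets to fuller documents.
- The n = 250 in the Control group section names no stage, so it is not independent evidence for 500 randomised.
- Additional file 1, Figure S1, is not shown and might give numbers by stage. It could not make the conflicting sentences agree.

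**Conclusion.** The inconsistency is real. Study design and the Abstract give 500 as the number randomised, whereas Recruitment and Sample size give 500 as what remains of 625. With post-entry attrition planned, both cannot be true. The attrition arithmetic itself is correct; the fault is that one figure labels two stages.

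If 500 are randomised, the plan's own losses leave about 400 complete cases, or about 425 if the 5% withdraw before allocation. Power would then be about 71% or 73% instead of 80%. This assumes a two-sided 5% test and that 500 completers give exactly 80%. It is a consequence on the plan's own terms, not a demonstrated loss for a defined effect.

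**What to change.** State three numbers separately and use them throughout: recruited, randomised and expected to complete.

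- **If 625 is intended:** say that about 625 are randomised (625 / 2 = 312.5, so 312 or 313 per arm). In the Abstract, Study design and Control group sections, relabel 250 per arm as expected completers. This costs only wording, since the 625 target is already in the plan. If some withdrawal is expected before allocation, say so and give the resulting number (594 if all 5% fall there).
- **If 500 is intended:** restate expected completers as about 400 (425 if only the 15% loss follows randomisation), and drop or explain the 625. Then recompute the power, or the detectable effect, in Sample size under the logistic mixed model, with a numerical effect, baseline prevalence and within-person correlation. The conditional 71% should not be copied in, because no planned effect is quantified. This costs one power calculation and no extra recruitment.

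If Figure S1 shows numbers by stage, bring it into line.

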### Recruitment

Study participants aged 50–69 years and insufficiently active (less than 150 minutes of moderate physical activity per week) [11] will be recruited. Additional criteria for metabolic syndrome is based on assessing the following International Diabetes Federation (IDF) metabolic syndrome criteria [5]: central obesity (waist circumference >94 cm men or >80 cm women [Europids, Sub-Saharan Africans, Eastern Mediterranean, Middle East]; >90 cm men or >80 cm women [South Asians, Chinese, Japanese]); plus any two of: raised triglyceride level (>1.7 mM, or treatment for this); reduced HDL-cholesterol (<1.03 mM in males and <1.29 mM in females, or treatment for this); raised blood pressure (systolic ≥130 mmHg or diastolic ≥85 mmHg, or treatment of previously diagnosed hypertension); raised fasting plasma glucose (≥5.6 mM). However, only one instead of two of the latter four conditions needs to be satisfied to increase the potential pool of at risk participants. Identifying participants at risk of developing metabolic syndrome will enable appropriate intervention to be implemented, with the aim of preventing the onset of the syndrome and potential for type 2 diabetes and cardiovascular disease [12].

The following exclusion criteria will apply: previous diagnosis of diabetes mellitus (other than gestational diabetes); receiving treatment to lower blood glucose; on a weight loss diet or having weight fluctuations of >5% within the past 6 months; involvement in another physical activity and/or nutrition program; or a partner/individual residing in the same household as another participant already recruited for the study (to avoid contamination).

After the initial screening (n = 1000), it is expected that 625 participants will be eligible to join the study. Allowing for a subsequent 5% withdrawal rate and another 15% loss to follow-up, a final sample size of n = 250 intervention and n = 250 controls is anticipated, with quota sampling to ensure equal numbers of males and females. These figures are based on the pilot recruitment and data collection phase of the study.

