Once eligibility criteria are determined, random assignment to intervention and control groups will occur, with quota sampling for gender. Suburbs and postcodes will be ranked according to the Socio-Economic Index for Areas and equal numbers of low and high scoring suburbs and postcodes will be allocated to each group. Intervention participants will be briefed about the purpose of the control group and the importance of refraining from communication about the program with control group members during the intervention period. They will receive the intervention materials and their AUSDRISK scores to emphasise the relevance of the program and the need for compliance to the lifestyle intervention.

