**Table 1 Tab1:** **Summary of outcome variables**

***Outcome variable***	***Measuring instrument***
Metabolic syndrome diagnosis/status	IDF criteria [5]
Glucose, triglyceride, cholesterol (total, LDL, HDL, non-HDL)	Blood samples [27]
Blood pressure	OMRON automatic BP monitor
Anthropometric measurements (BMI, waist circumference, waist-to-hip ratio, body fat and muscle percentage)	Body composition scale, stadiometer, measuring tape [28,29],
Physical activity (programmed, incidental)	ActiGraph GT3X Accelerometer [30]
Sedentary and physical activity behaviours	IPAQ [13]
Diet (fat, fibre, fruit, vegetable consumption)	Fat & Fibre Barometer [31]
Economic analysis	EQ-5D-3 L [32]

*Metabolic syndrome status* will be determined using the IDF criteria [5]. Participants satisfying the full criteria will be classified as having metabolic syndrome; whereas those with central obesity (waist circumference >94 cm men or >80 cm women [Europids, Sub-Saharan Africans, Eastern Mediterranean, Middle East]; >90 cm men or >80 cm women [South Asians, Chinese, Japanese]) plus any one of: raised triglyceride level (>1.7 mM, or treatment for this); reduced HDL-cholesterol (<1.03 mM in males and <1.29 mM in females, or treatment for this); will be classified as being at risk of metabolic syndrome. Post-test reclassification will determine changes to metabolic syndrome status after 6 months.

*Blood samples* will be taken by a phlebotomist at baseline and 6 months to measure a range of markers of cardiovascular disease risk and metabolic syndrome status. Fasting plasma glucose will be measured to assess insulin sensitivity. Fasting lipid levels will also be determined to assess lipid profile and CVD risk. The concentrations of triglycerides, total cholesterol and HDL cholesterol will be measured allowing determination of total-, LDL-, HDL-, and non-HDL-cholesterol levels [27]. All blood tests will be performed by Western Diagnostic Pathology.

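### As printed, the glucose criterion has no treatment or diagnosis clause, so post-test reclassification can score a participant treated for new diabetes as improved (minor)

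*Protocol article*

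**What the plan says.** The protocol article prints the metabolic syndrome components in full once, under Recruitment, and attributes them to the International Diabetes Federation (IDF) criteria. Besides central obesity there are four:

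- Triglycerides: "raised triglyceride level (>1.7 mM, or treatment for this"
- HDL-cholesterol: "reduced HDL-cholesterol (<1.03 mM in males and <1.29 mM in females, or treatment for this"
- Blood pressure: "raised blood pressure (systolic ≥130 mmHg or diastolic ≥85 mmHg, or treatment of previously diagnosed hypertension"
- Glucose: "raised fasting plasma glucose (≥5.6 mM"

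The full syndrome needs central obesity and two of the four; entry to the trial needs only one. The same section excludes people with a "previous diagnosis of diabetes mellitus (other than gestational diabetes" and people "receiving treatment to lower blood glucose".

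Outcome measures, in the text below Table 1, determines metabolic syndrome status by the IDF criteria, with the same reference number. It then states: "Post-test reclassification will determine changes to metabolic syndrome status after 6 months". It does not reprint the glucose or blood pressure item. Its at-risk class is central obesity plus raised triglycerides or reduced HDL-cholesterol only.

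**The concern.** Three of the four components carry a treatment alternative and the fourth does not. At baseline nothing is lost, because anyone whom such a clause would catch is excluded. The exclusions act at entry only. Once the criteria become an outcome at 6 months, a participant can have been diagnosed and treated in the meantime, and the printed rule then looks only at the measured value.

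The situation is foreseeable. Participants are screened for high risk of type 2 diabetes (AUSDRISK score of 12 or more), fasting glucose is measured at screening, only a previous diagnosis excludes, and no upper glucose limit for entry is stated. What is at stake is the direction of the error: some participants who progress to the disease the trial hopes to prevent would be recorded as having improved in metabolic syndrome status.

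**Working it through.** The document gives no figure on this point to reproduce. The recruitment figure in Sample size does reproduce, 500 / (1 − 0.20) = 625, and this point does not affect it. The check is a complete listing of cases under the printed rules.

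**Inputs.** Components and entry rule come from Recruitment. The at-risk class and the post-test reuse come from Outcome measures.

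**Case examined.** Glucose is 5.6 mM or more at baseline. Diabetes is diagnosed and treated during the trial, and glucose is below 5.6 mM at post-test. Central obesity persists and the other three components do not change. Those three can each be present or absent, which gives 2 × 2 × 2 = 8 patterns.

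**Rule.** Two or more components: metabolic syndrome (MetS). Exactly one component: at risk under Recruitment (any of the four); under Outcome measures, at risk only if that component is triglycerides or HDL-cholesterol. Otherwise: neither.

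| Other components present at both visits | Patterns | Recruitment at-risk rule | Outcome measures at-risk list |
|---|---|---|---|
| None | 1 | at risk → neither | neither → neither |
| Blood pressure only | 1 | MetS → at risk | MetS → neither |
| HDL only | 1 | MetS → at risk | MetS → at risk |
| Triglycerides only | 1 | MetS → at risk | MetS → at risk |
| Any two | 3 | MetS → MetS | MetS → MetS |
| All three | 1 | MetS → MetS | MetS → MetS |

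**Result as printed.** A better class is recorded in 1 + 3 = 4 of 8 patterns under the Recruitment rule, and in 3 of 8 under the Outcome measures list.

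**Result with a clause.** If the glucose component counts as met after a diagnosis or start of treatment, the post-test class equals the baseline class in every row, so 0 of 8 patterns improve.

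**Two limits.** The patterns are not weighted by how often they occur, so 4 of 8 and 3 of 8 are not rates. If glucose was below 5.6 mM at baseline, treated new diabetes with a post-test value below 5.6 mM gives no false improvement; the worsening is simply not recorded.

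**The case against.** The strongest reply is that the quoted list belongs to Recruitment, where a glucose treatment clause would be redundant. Outcome measures refers to the IDF criteria and their full form without reprinting the glucose item, and the cited source may contain a clause. This stands in part: it cannot be said that the source lacks one. But Recruitment presents its list as those criteria, it is the only version printed, and Outcome measures gives the same reference with nothing added. A reader who scores from the article would apply the rule without a clause.

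A reader might also infer more than the document supports:

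- **That many participants are affected.** False improvement needs raised baseline glucose, a value below 5.6 mM on treatment at post-test, and at most one other component. No rate of new treatment over 6 months is given, so any count would be invented.
- **That the arms are biased against each other.** Of intervention participants the Procedure section says "They will receive the intervention materials and their AUSDRISK scores to emphasise the relevance of the program", and controls do not receive their scores; scheduled telephone calls are also part of the intervention only. Different care-seeking is therefore conceivable. But all participants are told the aims of the research, controls are told that they are eligible, and nothing is said about drug starts. A difference in treatment uptake remains conjecture.
- **That the main outcome is compromised.** Metabolic syndrome status heads Table 1, but that is list order. The article names no primary outcome, the power calculation uses physical activity participation, and the hypothesis in the Background names insulin sensitivity, lipids, anthropometry, activity and nutrition, with metabolic syndrome risk as what follows from them.
- **That the lipid and blood pressure clauses are also wrong.** Counting a treated component as abnormal is how the article presents the criteria. A further reclassification on measured lipid and blood pressure values would be a preference, not a correction.

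**Conclusion.** The point holds as a minor defect in the definition of one outcome. On the only criteria printed, a participant with raised glucose at baseline who is diagnosed, treated and below 5.6 mM at 6 months loses the glucose component. With exactly one other component, that person leaves the metabolic syndrome class; with glucose alone, the person moves from at risk to neither under the Recruitment rule. The at-risk list in Outcome measures gives different results in two rows of the table, so the two sections also have to be reconciled.

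The number affected cannot be computed from the document. It is probably small, given the conditions that must coincide. The conclusion assumes that the Recruitment wording is what will be applied at post-test, that central obesity persists, and that the other components are unchanged. Neither the sample size nor the power calculation is affected.

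**What to change.** In Outcome measures, add one sentence: for post-test reclassification, the glucose component counts as met for any participant diagnosed with diabetes or started on glucose-lowering treatment after baseline. This concerns scoring only and changes nothing in anyone's care. If the sponsor already reads the cited criteria this way, the sentence simply makes that explicit.

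Repeat the entry questions on diabetes diagnosis and glucose-lowering treatment at post-test in both arms. All participants already complete a questionnaire at that visit, so the cost is one more item.

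In the same edit, reconcile the at-risk list in Outcome measures (triglycerides or HDL-cholesterol only) with the one-of-four rule in Recruitment, so that participants are classified by one rule at both visits.
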